## **Relevance**

To the knowledge of the authors, there has not been any study on the reliability of CPM with the nociceptive withdrawal reflex. Because this measurement is a reflex, and hence not dependent on subjective perception, more precise information and less variability in regard to spinal pain modulation is expected. Most studies on CPM have involved psychophysical QST measures, leaving a subjective error margin in the measured effects. If reliability of the CPM with the nociceptive withdrawal reflex can be established, this assessment could find increasing applications in clinical practice and research. By studying three different CPM measures, we will also be able to compare the reliability of electrophysiological and psychophysical CPM measures. Detection of individual disturbances in CPM may allow the development of mechanism-based interventions in pain therapy as well as a better understanding of the underlying physiopathology of chronic pain syndromes.

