### **Aims**

The primary aim of the present study is to assess the reliability of CPM using the nociceptive withdrawal reflex as test stimulus and the ice water test as conditioning stimulus in 34 consecutive patients, with a 7 days interval between two sessions.

Secondary aim is to compare the reliability of CPM with the nociceptive withdrawal reflex to the reliability of CPM assessed with subjective pain assessments, i.e. pain threshold and pain intensity after electrical stimulation.

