#### **b. Reliability**

The sample size for a test-retest reliability study depends on the minimally acceptable level of reliability  $\rho_0$ , the target level of reliability  $\rho$  (measured as intraclass correlation coefficient), and the number of repetitions of the measurement  $n$ . The values for type I and type II errors ( $\alpha$  and  $\beta$ ) are set to 0.05 and 0.20, respectively [22]. Considering a minimum number of measurements of  $n = 2$  (one measurement per session and two different sessions), reliability values of  $\rho_0 = 0.5$  as the minimally accepted reliability and  $\rho = 0.8$  as the expected reliability [10] [23], the minimum sample size for this experiment is 22 subjects.

In summary, 34 subjects are required in order to detect CPM and estimate test-retest reliability.

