### **Statistical Analysis**

The between-session reliability (also referred to as *stability over time*) of the nociceptive withdrawal reflex to single electrical stimulation will be assessed using multiple methods described below.

- *Intraclass correlation coefficient (ICC)*: it measures the relative homogeneity within sessions in relation to the total observed variation between sessions. For this analysis, a two-way mixed model using absolute agreement will be selected, and ICC for single measurements will be reported. ICC values above 0.75 are indicative of good reliability [24]. An  $F$  test with a hypothesized ICC value of 0.5

(representing a fair reliability level) will also be carried out in order to determine if the ICC values obtained are significantly different from this level.

- *Coefficient of variation (CV)*: it represents the standard error of measurement expressed as a percentage of the subject's average threshold. The CV can be interpreted as the percentage of deviation from the average threshold below which 68% of the differences between sessions may be expected to lie [25].

- *Bland-Altman agreement analysis*: it is based on the analysis of the average vs. the difference of the thresholds between two given sessions, from which the so called *limits of agreement (LA)* can be derived, as the average difference  $\pm 1.96$  times the standard deviation of the differences. The LA delimit the range within which 95% of the differences between thresholds in two single sessions may be expected to lie. In close relation to this definition, the *coefficient of repeatability (CR)* is defined as the value below which 95% of the *absolute* differences between thresholds in two single sessions may be expected to lie. If there is no systematic bias in the thresholds between sessions, the average difference between thresholds is expected to be zero, and the LA and the CR should be similar [26].

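### The secondary aim compares reliability between reflex and psychophysical CPM, but the analysis section covers only the reflex and gives no way to compare two ICCs from the same subjects

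*Protocol*

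**What the plan says.** The Aims section states: "Secondary aim is to compare the reliability of CPM with the nociceptive withdrawal reflex to the reliability of CPM assessed with subjective pain assessments". The subjective assessments are the electrical pain threshold and the pain rating after suprathreshold stimulation. The Relevance section repeats the promise: "we will also be able to compare the reliability of electrophysiological and psychophysical CPM measures".

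The Statistical Analysis section opens by saying that the between-session reliability "of the nociceptive withdrawal reflex to single electrical stimulation will be assessed using multiple methods described below". The methods are:

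- an ICC: "a two-way mixed model using absolute agreement will be selected, and ICC for single measurements will be reported", with the label "ICC values above 0.75 are indicative of good reliability";
- an F "test with a hypothesized ICC value of 0.5";
- a coefficient of variation (CV), as a percentage of the subject's average threshold;
- Bland-Altman limits of agreement and a coefficient of repeatability.

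The section names neither psychophysical measure and gives no contrast, interval or test between measures. The sample size rests on detecting a mean CPM shift and on one ICC against 0.5, with "one measurement per session and two different sessions". It concludes that "34 subjects are required in order to detect CPM and estimate test-retest reliability". A difference between ICCs does not enter into it.

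**The concern.** A comparative aim needs a statistic that contrasts the measures, and every listed tool describes one measure. Limits of agreement are in mA for the reflex and pain thresholds but in NRS points for the pain rating, so they cannot be compared for that pair. The CV has no unit, but it is defined relative to an average threshold, which a pain rating does not have. The ICC is the one listed statistic that carries over to all three measures.

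All three ICCs come from the same men, and the pain threshold is taken at the same time as the reflex threshold, so the estimates are dependent. If one ICC passes a cut-off and another does not, or one is simply larger, that does not show that the reliabilities differ. The Relevance section already expects less variability from the reflex, so a chance gap in that direction could be read as confirmation.

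**Working it through.** **1. The plan's own figures.** Both reproduce and are not in dispute.

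- Reliability: k = 1 + 2(z_α + z_β)²n / [(ln C0)²(n − 1)], with C0 = [1 + nρ0/(1 − ρ0)] / [1 + nρ/(1 − ρ)]. With n = 2, ρ0 = 0.5 and ρ = 0.8, C0 = 3/9 = 1/3. With one-sided α = 0.05 and β = 0.20, k = 1 + 4 × (1.645 + 0.842)² / (ln 1/3)² = 21.5, so 22.
- CPM detection: paired t-test, 2.0/4.0 = 0.5 SD, two-sided 0.05. Power is 79.5% at 33 subjects and 80.8% at 34, so 34.

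Neither calculation concerns a difference between two ICCs.

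**2. Precision of one ICC at 34 subjects.** An observed ICC of 0.75 has a 95% interval of about 0.56 to 0.87, and one of 0.80 about 0.64 to 0.89. The F test against 0.5 rejects when MSR/MSE exceeds [1 + 2 × 0.5/0.5] × F(0.95; 33, 33) = 3 × 1.788 = 5.36. With no session shift that is an ICC of about (5.36 − 1)/(5.36 + 1) = 0.69.

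**3. Two measures with the same true ICC.**

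- From the protocol: 34 subjects, two sessions, two-way absolute-agreement single-measure ICC, label at 0.75, F test against 0.5.
- Assumed: normal data, no session shift, a one-sided 5% F test (the protocol does not state the side), and a between-measure correlation of 0.8 to 0 (the protocol gives none).
- The true ICC is varied. The protocol expects 0.8 in its sample size, while its Introduction reports very poor CPM reliability in low back pain patients.

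| True ICC of both measures | Opposite sides of 0.75 | F tests disagree |
|---|---|---|
| 0.4 | at most 0.2% | at most 2% |
| 0.5 | 1-2% | 7-9% |
| 0.7 | 23-40% | 28-49% |
| 0.8 | 21-36% | 9-13% |
| 0.9 | at most 0.5% | about 0.1% or less |

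The lower end of each range at 0.7 and 0.8 belongs to correlation 0.8 and the upper end to correlation 0. Repeated runs differ by about one percentage point. The rates count both directions. By symmetry, the reflex alone clears 0.75 in about half of the discordant cases, so about 11-20% at a true ICC of 0.7.

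**4. ICCs set side by side, without cut-offs.** With equal true ICCs, the SD of the difference between the two estimates is 0.08-0.13 at 0.7 and 0.13-0.21 at 0.4. At 0.4, gaps above 0.2 arise by chance in 11-33% of studies.

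**5. A direct paired comparison.** A jackknife over subjects of the difference in Fisher-z ICCs, with 34 subjects, gave a false-difference rate of 4-6% at equal true ICCs of 0.5, 0.7 or 0.8. Its power was:

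| True ICCs | Correlation 0 | 0.5 | 0.9 |
|---|---|---|---|
| 0.8 vs 0.5 | 57% | 68% | 99% |
| 0.8 vs 0.7 | 15% | 19% | 50% |

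**The case against.** Only the protocol is at hand, and the method for a secondary comparison could be left to a statistical analysis plan. That would be decisive if the protocol were silent. It is not: it fixes an ICC model, a label, a test and two further methods, confines them to the reflex, and then asserts that the study can make the comparison. The mismatch lies within the document.

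Four stronger readings are tempting, and the protocol does not support them:

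- A reader might infer that the comparison will be made by classing each ICC. No section says so. The ICC is to be reported and 0.75 is an interpretive label, so estimates side by side are equally compatible. The cut-off rates above show what classing would do, not what is planned.
- A reader might infer that false differences would be frequent whatever the true reliability. Under either rule this holds for true ICCs near 0.7 and, for the 0.75 label, at 0.8. If all measures are poor or all are excellent, they usually share a class.
- A reader might infer that limits of agreement are useless throughout. The reflex and pain thresholds are both in mA, so their limits share a unit. The obstacle applies to the pain rating.
- A reader might take 1.96 × the SD in step 4 (about 0.16 to 0.25 at a true ICC of 0.7) as a fixed resolution limit. It bounds chance variation at one assumed ICC and is not a detectable difference. Even a true gap of 0.3 (0.8 vs 0.5) is found with only 57-68% power at correlations of 0 to 0.5.

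The primary aim and the sample size of 34 are not affected.

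**Conclusion.** The point holds in this limited form. The protocol sets a comparative secondary aim and claims the ability to meet it, but its analysis section is written for one of the three measures and contains no inference on a difference between dependent ICCs.

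The size depends on true ICCs and a between-measure correlation that the protocol does not give. At the protocol's own expected ICC of 0.8, two equally reliable measures would be labelled differently at 0.75 in about 21-36% of studies and split by the F test in 9-13%. At 0.4 or below, or at 0.9, such splits are rare. A valid interval is still needed at low reliability, where chance gaps between ICCs are widest. This is a correction that should be made to a secondary aim; it does not threaten the primary result.

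**What to change.** In Statistical Analysis, extend the ICC analysis to all three CPM measures. Estimate ICC(reflex CPM) minus ICC(pain-threshold CPM) and ICC(reflex CPM) minus ICC(pain-rating CPM), each with a 95% confidence interval. Obtain the intervals from a bootstrap or jackknife that resamples whole subjects, so that all of a subject's measures and both sessions stay together. Claim a difference only if the interval excludes zero.

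In Relevance, say that the comparison is an estimate with limited precision at 34 subjects: about 57-68% power for ICCs of 0.8 and 0.5 at between-measure correlations of 0 to 0.5. Do not state a fixed smallest resolvable difference.

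The cost is a few lines of analysis code and a more modest sentence. No further subjects or measurements are needed.

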## **Varia**

### **Risks**

No risks related to the test procedures are known.

### **Ethical aspects**

The pain measurements have been performed by our group for many years on several hundreds of subjects. They are well tolerated and currently used with children starting at age 7.

### **Data storage**

The data will be stored in a locked-up drawer for 10 years at the University Hospital of Bern.

### **Financing and insurance**

This study is part of a project financed by the Swiss National Science Foundation (SPUM no. 33CM30\_124117) and the Scientific Funds of the University Department of Anesthesiology, Inselspital Bern, Switzerland.

The public liability of the investigators will be covered by the insurance of the Inselspital Bern.

### **Authorship**

Authorship for the project will be based on the Uniform Requirements for Manuscripts of the International Committee of Medical Journal Editors ([www.icmje.org/#author](http://www.icmje.org/#author)). According to these requirements, authorship credit should be based on 1) substantial contributions to conception and design, acquisition of data, or analysis and interpretation of data; 2) drafting the article or revising it critically for important intellectual content; and 3) final approval of the version to be published. Authors should meet conditions 1, 2, and 3.

Changes in the tasks of the authors listed below may lead to loss of authorship for some contributors or addition of new authors during the course of the project.

### **Time plan**

Patients recruitment: from Mai 2012 to September 2012

Data analysis: November 2012.

First draft of paper: January 2013.

Submission to peer-reviewed journal: March 2013.

